### Sample size

The sample size calculation was estimated on the basis of our feasibility study evaluating the effects of NF training on cognitive performances in MCI subjects (registered at ClinicalTrials.gov under the identifier: NCT03526692, on 16 May 2018). In an analysis of covariance study (ANCOVA), sample sizes of 20 are obtained for each of the three groups whose expected averages of TMT B are 140 in the control group and 105 s in two intervention groups with a standard deviation of 45. The supposed R-squared of the model is 0.20. The total sample of 60 subjects has a power of 80% to detect differences between means using an F test with a significance level of 0.05.

### Participants

Sixty older adults with MCI will be recruited by the geriatric medicine physicians through the outpatient memory service from Broca University Hospital in Paris. All participants will be eligible if they meet MCI criteria according to Petersen et al. [54]; are aged 60 years or over; have a Mini Mental State Examination (MMSE) [55] score > 24; a subjective memory complaint confirmed by an informant; perform at/or below 1.5 standard deviations from the mean for age and education-matched norms on more than one of the neuropsychological tests; preserve activity of daily living; and absence of dementia. The exclusion criteria will include patients with epilepsy, stroke, tumor, head trauma, personality disorders, and psychiatric disorders with the exception of mild depression using the GDS (Geriatric Depression Scale, normative score: normal 0–9, mildly depressed 10–19, very depressed 20–30) [56]. Participation in other trials will be prohibited during the study.

### Intervention

#### Neurofeedback training

Researchers have improved NF methodology, especially the determination of the criteria for the best use of this technique. We consider some essential technical aspects: the quality of the signal, the choice of the reward threshold, the type and number of positive reinforcements, the number of sessions, the duration of a session, task instructions and motivation given to the subject before and after the training session [45].

The sensorimotor rhythm is activated in central brain regions [57, 58]. Thus, EEG signals for SMR/delta-ratio training will be recorded from channel Cz according to the International 10–20 system and the instructions in the SMR NF protocol which suggest recording from C3, C4 or Cz. A-32 channel system (EEGDigiTrack Biofeedback Plus module, Inc. Elmiko Medical sp. z. o. o. (Ltd), Warsaw, Poland) will be used for SMR NF training. The delta rhythm is also recorded and, in this case, SMR is stimulated while delta waves are suppressed to avoid sleep.

For the second NF protocol beta1 (12–21 Hz)/theta (4–8 Hz), we aim to decrease this ratio by promoting beta1 and reducing theta. Training will be recorded in Fz, according to the international 10–20 system [45].

The ground electrode will be recorded at the right mastoid and the reference at the left mastoid. All impedances will be maintained below 5 KOhms (kΩ) and two inhibit bands will be used to avoid the augmentation of the signals by muscle artifacts such as, movements, coughs, jaw contraction, eye blinks (0.5–2 and 43–59 Hz). When the beta2 rhythm amplitude level increases, it usually means muscular artefact or an increase in the patient’s stress and tension levels, so the EEGDigiTrack System will suggest training and suppressing it.

The NF experiment will consist of 30 sessions, twice or three times a week during a maximum of 4 months. From our previous pilot study described above and carried out by our multidisciplinary team (data unpublished), we noticed that the nature of the task in NF training was very important to keep motivation and concentration in our sample. To avoid sleepiness or annoyance, we chose to keep the video of historical reportage as a NF task that had been unanimously appreciated. Thus, during the 30 sessions, videos of historical reportage will be watched for 40 min, divided in eight rounds of 5 min with 20-s break between. Session will last 45 min (Fig. 2). The breaks prevent drowsy episodes and permit the recommencing of sustained attention. The rest of the video will be shown at the next training. The subject receives visual and auditory feedback. To modulate brain activity in the SMR frequency band or in the beta1 band, the video will indicate a bad contrast and a particular sound each time the thresholds are not reached. The degree of difficulty will be manually adjusted by defining the thresholds. As a second feedback, a horizontal bar will be presented on the corner of the patient’s screen showing their real-time SMR power, delta power, beta1 power and theta power according to the threshold. When the expected band power reaches the predefined threshold, the color of the bar will change from red to green. Participants are instructed to try to voluntarily increase this bar to the green color. Neurofeedback training will be conducted by a PhD candidate experienced in neuropsychology, neurophysiology and NF.

**Fig. 2 Fig2:**
[figure not shown]
Description of a 40-min neurofeedback session with a historical reportage. Note reference: EEGDigiTrack, Inc. Elmiko Medical

A few conditions are recommended during training. For example, the room should be as quiet as possible and shaded; fluorescent lighting during the training must be avoided since it may cause interference; the patient should be at about 1.5 m from the monitor; the patient’s chair has to be stable with a headrest and should allow the patient to be in a comfortable position for muscle relaxing; only the technician and the patient are allowed to be in the room during the NF trainings.

#### Control group condition

Control group will receive a psycho-pedagogical program within the hospital, at the same frequency as experimental group. Each session will be organized using the same video material as for the NF training sessions. We will suggest that participants watch a historical report for 40 min with the recommendations to focus on dates, proper names and topics, then to answer verbally questions pertaining to the historical report for the last 20 min. As with the experimental group, the control group will undergo questionnaires, EEG recording and neuropsychological assessments at three time points: pre-training (T0), post training (T1) and follow-up (T2).

### Assessments

#### Cognitive outcomes

Neuropsychologists involved in data collection at any point of the assessment will be blinded to the condition assignment of each participant. They will complete cognitive assessments and questionnaires with a trained neuropsychologist blinded to the participants’ training condition, at baseline (T0), after the last NF training session at 4-month (T1) and at 3-month follow-up (T2), (see Fig. 2). Assessment duration will be done in one session for approximately 2 h in order to measure cognitive performances (see Table 1). Alternative test versions or forms will be used during post-NF training when possible to avoid learning effects due to repeated tests. Mood will be assessed by the Geriatric Depression Scale (GDS), a brief 30-item questionnaire to monitor depression over time in clinical settings [56]. Anxiety will be assessed with the Goldberg Anxiety Scale, the most commonly used rating scale to measure the severity of perceived anxiety symptoms [59].

**Table 1 Tab1:** List of neuropsychological tests administered in pre and post-neurofeedback (NF) training

Neuropsychological test		
Global assessment of cognitive functions	Cognitive function	Description
• MoCa (2 versions) (range from 0 to 30)	Visuospatial/executive	Score between 21 to 25 = MCI
	Naming	
	Memory	
	Attention	
	Language	
	Abstraction	
	Orientation	
• MMSE (range from 0 to 30)	Brief quantitative cognitive measures	Score between 23 and 26/30 = MCI
	Orientation	
	Registration	
	Attention	
	Calculation	
	Recall	
	Language	
Episodic memory		
• RAVLT (4 lists of 15 words)	Declarative memory	A 15-noun word list, ability to encode, combine, store and recover verbal information
• Story Recall Test (A or B) recalls and a	Declarative memory	2 immediate delayed recall (30 min)
• DMS 48	Visual recognition memory	1st phase: implicit encoding 48 visual items and immediate recall; 2nd phase: 1 h delayed trial on choice recognition
• Rey-Osterrieth Complex Figure (or Taylor Complex Figure)	Visual declarative memory	30-min recall
Working memory and executive functions		
• TMTA (Trail Making Test part A)	Sustained attention	Capacity to maintain and attentional activity over a period of time
• TMTB (Trail Making Test part B)	Alternating attention	Capacity to shift in focus and tasks (B/A time)
• eCT	Executive function	Capacity to discriminate stimuli

Note: *MCI* mild cognitive impairment, *MoCa* Montreal Cognitive Assessment, *MMSE* Mini Mental State Examination, *RAVLT* Rey Auditory Verbal Learning Test, *DMS 48* Delayed Matching-to-Sample 48 items, *TMTA&B* Trail Making Test part A and part B, *eCT* Tablet-PC-based Cancellation Test. Rey, A. Story Recall [63]

#### Primary outcome

The primary outcome will be the change in attention measured by the Trail Making Test (TMT) part B between T0 and T2 compared to the control group. The TMT consists of measuring the time of the test performances [60, 61]. In TMT B, numbers and letters have to be alternately connected in the shortest time.

#### Secondary outcomes

The secondary outcome will include:

The changes in cognitive functions between T0 and T2 measured by:
The score in part A of the Trail Making Test (TMT A), the number of errors in part A and B and the differences between B and A (B − A). In TMT A, 25 numbers have to be randomly distributed in sequential order as fast as possibleThe Rey Auditory Verbal Learning Test (RAVLT) assessing episodic memory. We will consider two performances: (1) the total learning score: the sum of all correct responses across five consecutive trials, (2) the delayed recall score: the number of correct responses at the last trial. The test consists in reading 15 words aloud to a participant who has to recall them freely. Four more consecutive learning trials are then performed in the same way. The word presentation order remains fixed across trials. After a 20-min delay period, the evaluator asks the participant to recall the words for the last time [62]The Story Recall Test assessing declarative memory. The test consists in reading a story with two immediate recalls and a delayed recall after 30 min [63, 64]The Delayed Matching-to-Sample 48-item (DMS 48) assesses visual recognition memory. The first phase is an implicit encoding of 48 visual items and an immediate recall. The second phase is a 1-h delayed trial on choice recognition [65]The Montreal Cognitive Assessment (MoCa), measures global cognitive efficiency whose visual/spatial, naming, memory, attention, language, abstraction and orientation [66, 67]The Mini Mental State Evaluation (MMSE) is a brief quantitative measure assessing orientation, registration, attention, calculation, recall and language [55]The Backward Digit Span of the Wechsler Adult Intelligent Scale-Fourth Edition (WAIS-IV) assesses working memory, processing speed/attention control [68]The Verbal Fluency (P letter, 2 min; animals, 2 min) measures verbal ability and executive control [69]The Rey-Osterrieth Complex Figure (ROCF) assesses planification/organization and visual memory and visual memory with a delayed recall (30 min) [70, 71]The Tablet-PC-based Cancellation Test (eCT) assesses executive function. It consists of simultaneously targeting stimuli while ignoring distractors as quickly as possible [55, 60, 67]Anxiety and depression will be assessed with the Goldberg Anxiety Scale and the Geriatric Depression Scale (GDS) [56, 59]

In order to reduce the risk that the test performance improvement may be due to learning effect of repeated assessments, we will use parallel versions of tests when available.2)The changes in EEG activities in a resting state after SMR/delta NF training and/or alpha/theta-ratio NF training in treatment groups compared to the control subjects

#### EEG data acquisition

Electroencephalography will be recorded by a technician in EEG and EEG data will be analyzed by a neurophysiologist “blinded” to the participants’ training conditions. Neurofeedback training sessions will be performed by a doctoral student trained in EEG and EEG NF application.

For each participant, EEG will be recorded and an EEG power spectrum will be calculated in pre- (T0) and post-NF training/psycho-pedagogical care at T1 and T2. We will use an electrocap of 19 scalp locations (Electro-cap, International Inc. Elmiko Medical, Warsaw, Poland) according to the international 10–20 EEG placement system, in FP1, Fp2, F7, F3, Fz, F4, F8, T3, C3, Cz, C4, T4, T5, P3, Pz, P4, T6, O1 and O2 with reference at the left mastoid and the ground at the right mastoid. The recording will use the sampling frequency of 500 Hz and band-pass filter (0.01–100 Hz). Multichannel amplifier (EEGDigiTrack SimplEEG32, Inc. Elmiko Medical Sp. zo.o. Ltd., Warsaw, Poland) will be used. Impedance will be kept below 5 KΩ for EEG. EEG artifacts will be automatically rejected. Then, two baseline conditions will be recorded such as the eyes-open baseline (EOB) condition and an eyes-closed baseline (ECB) condition. Each condition will last for 5 min and will be repeated three times (30 min recording in total). During the EOB condition, participants will be required to minimize blinking to avoid eye-movement artifacts. During the ECB condition, participants will be asked to close their eyes but stay awake.

The power of the EEG rhythms, such as theta (4–7 Hz), alpha (8–12 Hz), SMR (12–15 Hz), low beta (13–20 Hz) and high beta (20–30 Hz) will be computed from the moving averaged EEG power spectra. The EEG data in pre-NF training and post-NF training will be analyzed offline using MATLAB R2011b.

#### Risks and side effects

EEG recording has no risks except skin irritation caused by cleaning the scalp with abrasive cleaning gel. EEG acquisition and NF equipment do not send an electrical current and only electrical output is recorded from the sensors. All equipment used in this research are certified as medical devices (class IIa. EU) for use with human subjects.

EEG NF has no medical risk and side effects are seldom observed but if they are they usually only include headache, fatigue and mild anxiety. They are quickly remediable and are explained by the difficulties of the NF training and concentration retention.

### Methods against bias

In order to guarantee blinded treatment allocation, an independent statistician engineer, not engaged in this investigation, will carry out randomization. Applying equal allocation ratios to all three conditions, the process will be stratified. Statistical analyses will be conducted using the conservative intent-to-treat population in order to avoid statistical bias. Primary and secondary outcomes, and EEG recordings will be assessed by trained investigators and technicians who will be blind to the patient’s study status.

Effect sizes and confidence intervals will be calculated as Standardized Mean Change Index for within-group comparisons and as Standardized Mean Index difference for between-group comparisons and corrected for small sample sizes.

### Data management

Technical specifications of the trial database, such as variable names, age, disease, frequency of visits and sessions will be predefined and documented in the database manual and in the electronic Case Report Form. All information on the Case Report Forms will be confidential and traceable to source documents in the patient’s file; the original documents will be kept by the main investigators of the study at the Broca University Hospital in Paris. At the end of the study, personal information will be deleted. The final trial dataset and disclosure of contractual agreements will be kept at the Broca University Hospital in Paris. Interim analyses on the acquired data will be conducted and presented in meetings and conferences. Results of the final analyses will be presented at scientific conferences and published in scientific journals.

### EEG analysis

EEG data will be processed with MATLAB R2011b, MathWorks Inc., Natick, MA, USA.

We will calculate the power spectral density of EEG signals to extract the relative power (RP) and absolute power (AP) for each frequency band. By definition, the RP is a value that compares the AP within a frequency band with the total AP. So, relative theta, relative alpha, relative SMR and relative beta will be calculated in the central, frontal and temporal areas during the rest ECB and rest EOB conditions in pre-NF and post-NF training. The ANCOVA model will provide the differences in RP between these two times. When the difference is positive, it means that the RP in post-NF training for that channel is larger than the RP in pre-NF training. The variables will be used to assess differences between the SMR NF group and the control group.

The time schedule and analysis plan are illustrated in Table 2.

**Table 2 Tab2:** Analysis plan and time schedule

Activity/month	Responsible	1st year				2nd year												3rd year				
		1	5	9	11	13	14	15	16	17	18	19	20	21	22	23	24	25	26	27	28	29
Project development	Main investigators	x	x	x	x																	
Ethical Committee approval	Main investigators		x																			
Protocol preparation	Main investigators	x	x	x	x																	
Recruitment	Main investigators					x	x	x	x	x	x											
Informed consent	Main investigators					x	x	x	x	x	x											
Participants selection	Main investigators					x	x	x	x	x	x											
Information meeting with patient	Main investigators					x	x	x	x	x	x											
Randomization	Engineer in biostatistics										x											
Neuropsychological assessments	Neuropsychologists										x				x			x				
Questionnaire assessments	Neuropsychologists										x				x			x				
Electroencephalography recording	Technician specialized in EEG										x				x			x				
Neurofeedback training intervention	Main investigators										x	x	x	x	x							
Data collection	Main investigators					x	x	x	x	x	x				x							
Data analysis	Engineers in biostatistics										x				x			x	x			
Hypothesis testing	Main investigators + engineers in biostatistics														x			x				
Results and conclusion	Main investigators														x	x	x	x				
Dissemination of results (publication, conference, presentations)	Main investigators										x				x	x	x	x	x			

*EEG* electroencephalography

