9pt?>Neurofeedback training seems to be a promising aproach in patients with AD or neurological disorders if this technique is adapted to elderly patients with MCI. On this basis, it would be relevant to further this technique in subjects at risk of developing AD. Based on the studies of Reichert et al. [47], Kober et al. [40] and Luijmes et al. [53], our objective is to examine: (1) the effects of SMR/delta NF training and the beta1/theta-ratio protocols on attention and memory performances in subjects with MCI, (2) to verify whether MCI patients exhibit a decrease or an increase in EEG activities in a resting state after SMR/delta NF training and/or alpha/theta-ratio NF training and (3) to assess the effects of the two training protocols on other cognitive and mood measures.

We hypothesize that (1) central frontal beta1/theta-ratio NF training might be effective in improving attention capacities whereas the SMR/delta protocol in Cz might be effective in improving memory performances and (2) changes in EEG patterns in post-SMR/delta-ratio and beta1/theta-ratio NF training would be observed in the intervention group but not in the control group. This paper has been conceived under consideration of the spirit guidelines (Additional file 1).

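### The EEG analysis section names only the SMR arm versus control, whereas the EEG hypothesis and secondary outcome cover both neurofeedback arms; delta is missing from the listed bands and the second protocol is mislabelled.

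*Protocol article*

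**What the plan says.** The second hypothesis, at the end of the Neurofeedback part of the Background, predicts that "changes in EEG patterns in post-SMR/delta-ratio and beta1/theta-ratio NF training would be observed in the intervention group but not in the control group". The Secondary outcomes section defines the EEG outcome as "The changes in EEG activities in a resting state after SMR/delta NF training and/or alpha/theta-ratio NF training in treatment groups compared to the control subjects". Both cover more than one trained group.

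The EEG analysis section starts broadly. It will "extract the relative power (RP) and absolute power (AP) for each frequency band". It then narrows: "relative theta, relative alpha, relative SMR and relative beta will be calculated in the central, frontal and temporal areas", with eyes closed and eyes open, before and after training. An ANCOVA is applied to the change in relative power, and the section's only named group comparison follows: "The variables will be used to assess differences between the SMR NF group and the control group".

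The EEG data acquisition section has its own list: "The power of the EEG rhythms, such as theta (4–7 Hz), alpha (8–12 Hz), SMR (12–15 Hz), low beta (13–20 Hz) and high beta" (the last at 20–30 Hz). It places recordings at T0, T1 and T2. The Neurofeedback training section says of the SMR/delta arm that "SMR is stimulated while delta waves are suppressed to avoid sleep".

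**The concern.** A specific analysis section normally governs its own outcome. Here it names a narrower comparison than the hypothesis and the outcome it serves. An analyst who follows it would compare SMR training with control and stop, leaving half of the EEG hypothesis without its between-group contrast. If the beta1/theta contrast were added after the data had been seen, a reader could not tell whether it had been planned.

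The other two points make this worse. One of the two bands trained in the SMR/delta arm is not listed for analysis. The beta1/theta arm is named in neither the EEG outcome, which says alpha/theta, nor the EEG contrast, which says SMR only.

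**Working it through.** The article gives no EEG effect size, standard deviation or power, so there is no EEG figure to reproduce. Its one design figure, 80% power for the TMT B F test, concerns another outcome, and nothing here depends on it. The check is a comparison of the sections.

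**Contrasts**

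| Place | Groups compared on EEG |
|---|---|
| Background, second hypothesis | SMR/delta and beta1/theta, each expected to change, against control |
| Secondary outcomes, EEG item | Treatment groups (plural) against control |
| EEG analysis, closing comparison | SMR against control |

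- Contrasts implied by the first two rows: 2. Contrasts named in the third: 1.
- Randomization gives 1:1:1 allocation and Sample size gives 20 per group. The arm without a named contrast is therefore 20 / 60 = one third of the patients.

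**Whether Statistical analysis fills the gap.** Its three-group ANCOVA sentence concerns neuropsychological performance and questionnaire scores, not EEG. A later sentence extends the analysis to all outcome measures at T0, T1 and T2, but names no EEG contrast. The paired t tests in that section are within-group and do not compare an arm with control. The general text points towards including the beta1/theta arm, the specific text points away, and nothing says which prevails.

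**Bands**

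| Band trained | Arm | In EEG data acquisition list (5 bands) | In EEG analysis list (4 bands) |
|---|---|---|---|
| SMR | SMR/delta | yes | yes |
| Delta | SMR/delta | no | no |
| Beta1 | beta1/theta | as low beta | as beta |
| Theta | beta1/theta | yes | yes |

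Three of the four trained bands are listed, and delta is the exception. For the beta1/theta arm both trained bands are listed, so what is missing there is the comparison, not the measurement.

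**Label.** The Abstract, Neurofeedback training and Statistical analysis all describe the second arm as beta1/theta. The second objective in the Background and the EEG secondary outcome say alpha/theta. No arm is trained on that ratio.

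**Time points.** EEG analysis speaks of two times, before and after training. EEG data acquisition uses the post-training label for both T1 and T2, and Statistical analysis covers all three visits. The EEG analysis wording is ambiguous, but read with these two sections it includes T2.

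**The case against.** The best defence is that the article, read as a whole, covers the beta1/theta arm. The outcome definition is plural, the general analysis statement reaches every outcome, and all arms have EEG recorded. A full list of bands is also detail that an article may leave to an analysis plan. This has force: the fault is an inconsistency, and it would be wrong to say that no analysis of that arm is intended. It does not remove the point, because the one sentence that names an EEG contrast excludes that arm, and a statement that does not mention EEG contrasts cannot be relied on to override it.

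Some stronger readings are tempting but not supported:

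- **That the EEG hypothesis cannot be tested for either protocol.** It predicts changes in EEG patterns and names no band or ratio. SMR against control on theta, alpha, SMR and beta power does test it for the SMR arm.
- **That delta is never computed.** One list is introduced as examples, and power is to be extracted for each band. Delta is unnamed, not ruled out.
- **That T2 is excluded from the EEG analysis.** The acquisition and statistical sections include it.
- **That the trained ratios must be the EEG outcomes.** No objective or outcome makes them so; that is a design preference.
- **That the TMT B result depends on the EEG comparison.** The article lists resting EEG as a secondary outcome and never as a check of target engagement. The primary ANCOVA does not use it.

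**Conclusion.** The point holds as an internal contradiction. The EEG analysis section names one of the two contrasts that the hypothesis and the secondary outcome call for. Followed literally, it leaves 20 of 60 patients without a specified EEG comparison with control. The missing delta band and the alpha/theta label are real but smaller inconsistencies.

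This rests on two assumptions: that the EEG section governs the EEG outcome where it and the general text differ, and that the planned 20 per arm is reached. If the general statement on all outcomes were meant to prevail, the beta1/theta contrast would be planned but the EEG section would still need correcting. This should be fixed; because EEG is secondary and the primary analysis is untouched, it is not critical.

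**What to change.** - In EEG analysis, fit the ANCOVA with all three arms, adjusted for the T0 value, and report each neurofeedback arm against control.
- State that the post-training assessments are T1 and T2, in line with EEG data acquisition and Statistical analysis.
- Add delta to both band lists with its limits. The Background gives 1–4 Hz in one place and 0.5–4 Hz in another, so the analysis range has to be stated.
- Replace alpha/theta by beta1/theta in the second objective and in the EEG secondary outcome.
- Optionally, add the trained ratios (SMR/delta at Cz, beta1/theta at Fz) as further EEG variables.

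The cost is wording and some code. EEG is already recorded in all three arms at 19 sites, including Cz and Fz, at 500 Hz with a 0.01–100 Hz filter. The downside is more secondary comparisons. If relative power is analysed once per band, area and recording condition, the count per post-training visit goes from 4 bands × 3 areas × 2 conditions × 1 contrast = 24 to 5 × 3 × 2 × 2 = 60. The results should be presented as secondary with that number in view.
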